### Randomization and blinding

3.6

Participant recruitment and enrollment will be conducted by the principal investigator ([name]). Allocation will follow an individual randomization scheme into three groups: (I) MIG program, (II) conventional psychology, and (III) conventional physiotherapy. The randomization sequence will be computer-generated by an independent researcher (IC) who is not involved in assessment or intervention procedures. To ensure allocation concealment, sequentially numbered, sealed, opaque envelopes will be used. Immediately prior to the first session, a designated researcher will open the corresponding envelope to determine participant allocation. All baseline assessments will be performed prior to randomization, and outcome assessors will remain blinded to group assignment. Due to the nature of the interventions, blinding of participants and therapists will not be feasible. At the end of the study, the effectiveness of blinding will be assessed by asking evaluators about their perceptions regarding participant allocation. The participant flow process is presented in Figure 1.

**Figure 1 F1:**
[figure not shown]
Study flowchart.

### Interventions

3.7

#### MIG program

3.7.1

Participants in this group will receive a protocol specifically structured to assess the motor component of the MIG program. The intervention will be delivered by physiotherapists with prior experience in MIG and additional training provided by an interdisciplinary team (psychologists, speech-language pathologists, and occupational therapists), ensuring standardization of the research protocol implementation. The motor component will be delivered in three weekly sessions, each lasting 50 min, over a period of five weeks, following a previously defined structure. *Although the MIG is conceived as an intensive interdisciplinary program, the present trial was designed to isolate and evaluate only its motor component; therefore, the dosage reported here refers exclusively to the physical therapy sessions and does not correspond to the total interdisciplinary workload of the complete MIG protocol.*

In all sessions of the motor component protocol of the MIG program, the child will wear the MIG Flex therapeutic suit. This suit provides proprioceptive input and postural support during motor activities. This resource serves a dual function by promoting bodily stability and improved motor organization, while reducing the cognitive load required for postural maintenance and movement coordination, thereby freeing attentional and cognitive resources that can be directed toward interaction, play, and communication. At the beginning of each session, the physiotherapist will place and adjust the MIG Flex on the child and then initiate the narrative designed for that session. The narrative will introduce the main character, the setting, and the temporal context (initial situation), as well as the problem, triggering event, or central challenge (initiating event). The character's feelings or emotions and the plan for problem resolution will also be explicitly presented; this plan will correspond directly to the motor activities the child must perform to “help” the character, together with psychoeducational components about emotions aimed at promoting generalization of concepts and strengthening cognitive flexibility by allowing the participant to recognize common principles across different symbolic situations. The narratives used in sessions 01 and 15 are described in Supplementary Material 1.

The entire protocol structure will be contextualized and guided by narrative grammar, which will organize the session stages: (I) movement preparation with active myofascial mobilization; (II) core strengthening; (III) motor skills circuit, including balance, coordination, strength, motor planning, and power; and (IV) contextualized target activity. For these stages, various pieces of motor circuit equipment will be used, such as cones, balls, and unstable surfaces. The program will include functional training of motor skills, involving multiple physical capacities (strength, endurance, balance, flexibility, agility, power, and conditioning) trained in an integrated manner through activities such as running, jumping, hopping, galloping, throwing, and kicking. Table 1 presents a technical description of the activities, in which the playful and narrative components will be used as engagement and task-contextualization strategies, while maintaining the structural elements necessary for replication of the intervention. Session delivery will be based on narrative grammar and psychoeducational components related to emotions, integrated into motor activities as a means of promoting greater engagement and meaning for the child. Task progression will follow a gradual increase in complexity, always accompanied by positive feedback and continuous encouragement. At the end of each session, the child will receive a home-based task to reinforce and consolidate the narrative elements addressed that day. An example of this material completed by the child is provided in Supplementary Material 2.

**Table 1 T1:** MIG program motor component protocol.

Week	Preparation of the movement		Skill				Target movement		
	Myofascial tracks (spiral line and functional line)	Core	Activity 01	Activity 02	Activity 03	Activity 04	Activity 05	Activity 06	Activity 07
			Balance/proprioception	Dynamic balance	Motor coordination/ Strength	MMSS	Motor planning	Power	Target activity
1	Functional reach with trunk rotation in bipedal standing	Trunk flexion (upper abdominal crunch) with anterior reach and target between the lower limbs.	Functional reach with ring removal in bipedal support.	Tandem gait in a straight line	Squat	Bilateral ball throw with return by the therapist.	Throwing and catching toward a vertical target	Stationary running on a trampoline	Running and jumping
2	Functional reach with trunk rotation in bipedal standing	Trunk flexion with rotation associated with a functional task.	Anterior functional reach in unipodal standing	Functional gait with cone transposition	Functional squat with displacement and alternating object collection using the feet.	Bilateral transfer of objects in a horizontal plane at eye level.	Throwing and catching a vertical target with lateral movement.	Lower limb power training with bipedal jumps	Baseball
3	Functional reach with trunk rotation in bipedal standing	Hip flexion in supine position with functional task of picking up with the feet.	Static balance training in bipodal support on unstable surfaces.	Zigzag gait with visual guidance on the ground.	Lunge	Resisted load traction in a horizontal plane with lateral transfer.	Jumping over obstacles with object transfer	Sequential bipodal jumps with changes of direction (front and side)	Sequential unipodal jumps guided by visual stimulus (path by color)
4	Functional reach above the head with object grasping in bipedal standing position.	Core stabilization in supine position with limb dissociation (Dead Bug pattern)	Static balance training in unipodal stance on an unstable surface.	Lateral gait training with obstacle crossing	Alternating stationary Lunge	Low-level locomotion (crawling) with obstacle crossing and object transfer.	Step-up and step-down with alternating support.	Burpee	Lateral displacement
5	Functional reach with trunk rotation in bipedal standing	Ventral plank with elbows and knees supported.	Stationary running with transition to unipodal stance on command.	Sequential unipodal jumps to discrete floor targets	Advancement with anteroposterior displacement	Locomotion using manual support with elevation of the lower limbs (wheelbarrow standard)	Passing and receiving the ball with the feet in therapist-participant interaction.	Rhythmic bipedal rope jumping	Goal kicking

MMSS, upper limbs.

The motor component protocol of the MIG program is grounded in the systematic integration of cognitive and behavioral strategies that constitute intrinsic elements of the method and are aligned with the principles of predictive coding and embodied cognition. These strategies aim to reduce sensorimotor unpredictability, facilitate action organization, and support the construction of more stable internal models during interaction with the environment. Operationally, MIG incorporates resources widely recommended in the literature for optimizing motor learning in children with ASD (9), including the use of visual supports, modeling, prompting, task modification, immediate and positive feedback, adjusted instructions, and varied practice schedules. The structured application of these elements seeks to promote greater engagement, facilitate retention, and enhance the generalization of motor and functional skills to meaningful everyday contexts.

#### Conventional psychology

3.7.2

Participants in this group will receive intervention delivered by psychology professionals, based on cognitive and behavioral techniques and Applied Behavior Analysis, characterizing conventional psychological treatment. The intervention will be delivered over five weeks, with 50-minute sessions twice per week, totaling 10 sessions. The protocol will focus on the development of emotional regulation skills, including recognition of basic emotions (happiness, sadness, fear, disgust, anger, and anxiety) and their expressions, identification of emotions in oneself and in others, as well as strategies for appropriate emotional expression and regulation. Sessions will follow a structured therapeutic script, with clinical flexibility according to individual needs, without direct approaches to motor training or motor functional goal attainment. Interventions will be conducted in standard treatment rooms at the Reabilitar Clinic, in Ribeirão das Neves, Minas Gerais, Brazil.

#### Conventional physiotherapy

3.7.3

Participants in this group will receive conventional neurofunctional physiotherapy intervention, characterizing the usual motor treatment available in clinical services. The intervention will be delivered over five weeks, with two weekly sessions lasting 50 min each. Sessions will follow a minimally standardized structure consisting of warm-up (5 min), motor skills training (20 min), balance training (10 min), ball-based activities (10 min), and cool-down (5 min), with clinical flexibility for adjustments according to individual participant needs. The intervention will not include the use of therapeutic suits, narrative structures, cognitive strategies, or systematically integrated interdisciplinary components. Sessions will be conducted in standard treatment rooms at the Reabilitar Clinic, in Ribeirão das Neves, Minas Gerais, Brazil.

### Outcome measures

3.8

#### Primary outcomes

3.8.1

The Test of Gross Motor Development–Second Edition (TGMD-2) will be used to assess fundamental motor skills (25, 26). This standardized instrument quantitatively and qualitatively evaluates 12 motor skills, subdivided into locomotor and object control skills. Scores are derived from the sum of raw scores converted into motor quotients, allowing for normative performance analysis. Its validity and reliability for the Brazilian population with typical development were established by Valentini et al. (27), with subsequent application in studies involving children with ASD (28).

The Canadian Occupational Performance Measure (COPM) will be used to assess functional goal attainment (29). This semi-structured interview allows parents to identify, describe, and prioritize treatment goals relevant to their child's occupational performance. Each goal is rated on a 10-point scale for importance, performance, and satisfaction. The instrument demonstrates validity, reliability, and sensitivity to clinical change (29, 30).

#### Secondary outcomes

3.8.2

The Pediatric Balance Scale (PBS) will be used to assess functional balance. The PBS consists of 14 items that evaluate progressively more complex tasks, simulating fundamental activities of daily living and challenges to static and dynamic balance. Each item is scored from 0 to 4, with total scores ranging from 0 to 56, where higher scores indicate better functional balance performance. Its psychometric properties have been validated for the Brazilian population, demonstrating adequate responsiveness (31, 32).

The ABFW Child Language Test will be used to assess functional communicative skills (33, 34). Based on systematic observation of spontaneous interaction, it allows quantitative and qualitative analysis of communicative acts, communicative means, and communicative functions, demonstrating sensitivity for assessing pragmatic language performance (33–35).

The Behavioral Observation Protocol (PROC) will assess communicative and cognitive skills through a structured play-based interaction situation (36). This instrument allows analysis of language development and symbolic play and is particularly useful for characterizing cognitive-communicative functioning patterns in children with developmental disorders (37).

The motor subscale of the Vineland Adaptive Behavior Scales (VABS) will be used to assess gross and fine motor skills through a parent-reported questionnaire (38). The VABS-II version presents adequate psychometric properties, with concurrent validity of 0.77 when compared with the Peabody Developmental Motor Scales (39).

The Developmental Coordination Disorder Questionnaire (DCDQ) will be used as a parent-reported screening tool for motor coordination difficulties in daily activities (40). The DCDQ consists of 15 items rated on a 5-point Likert scale and provides age-adjusted cut-off scores to identify children at risk for developmental coordination disorder. The instrument has demonstrated good validity and reliability and has been culturally adapted and validated for use in Brazil.

### Procedures

3.9

Assessments will be administered by four independent and blinded assessors (a physiotherapist, a psychologist, a speech-language pathologist, and an occupational therapist), according to the specific technical expertise required for each instrument. The PBS and TGMD-2 will be administered by the physiotherapist; the COPM and the DCDQ by the occupational therapist through parent interviews; the VABS by the psychologist through parent interviews; and the PROC and ABFW by the speech-language pathologist. Assessments will be conducted at three time points: baseline, immediately post-intervention, and three months after the intervention. Baseline assessments will be completed prior to randomization. Recruitment is expected to begin in September 2025 and continue until January 2026.

### Data analysis

3.10

Analyses will be performed using IBM SPSS Statistics software. Descriptive analyses will initially be used to characterize the sample in terms of age, sex, and level of support. Data distribution will be assessed using the Shapiro–Wilk test. Baseline group comparisons will be conducted using one-way analysis of variance (ANOVA) or Kruskal–Wallis tests, as appropriate. All analyses will follow the intention-to-treat principle. Linear mixed-effects models will be used to evaluate intervention effects over time, including group-by-time interaction terms. In the presence of significant interactions, *post hoc* analyses with Bonferroni correction will be performed. Missing data will be handled using maximum likelihood estimation within the mixed-effects models. A two-sided significance level of 5% (*p* < 0.05) will be adopted for all analyses.

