### Sample size

3.5

The sample size was set at 66 participants, distributed into three groups with 22 individuals in each group. Sample size determination was based on the findings of a previous investigation that analyzed the effects of the MIG program in children with ASD (10). The calculation considered an effect size of 0.87, derived from outcomes of the Canadian Occupational Performance Measure, a statistical power of 80%, a significance level of *α* = 5%, and an estimated attrition rate of 20% over time. The calculation was performed using G*Power software version 3.1 (24).

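### As most naturally read, the mixed model gives each arm its own baseline mean; using the pre-randomisation baseline would sharpen the treatment contrasts at almost no cost

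*Protocol article*

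**What the plan says.** The Data analysis section (3.10) of the protocol article fixes the model in one sentence: "Linear mixed-effects models will be used to evaluate intervention effects over time, including group-by-time interaction terms". Pairwise comparisons follow conditionally: "In the presence of significant interactions", Bonferroni-corrected post hoc analyses are run. Missing data are left to maximum likelihood within the model, and tests are two-sided at 5%.

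The Procedures section (3.9) counts baseline among the occasions: "Assessments will be conducted at three time points: baseline, immediately post-intervention, and three months after the intervention". The Randomization and blinding section (3.6) adds that "All baseline assessments will be performed prior to randomization".

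On baseline itself, section 3.10 plans significance tests: "Baseline group comparisons will be conducted using one-way analysis of variance (ANOVA) or Kruskal–Wallis tests, as appropriate". Nowhere does the article name baseline as a covariate or state that the arms share a baseline mean.

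**The concern.** With group, time and their interaction fitted over baseline, post-intervention and three months, the usual coding estimates nine cell means, three of them at baseline. The interaction contrast for two arms is then a difference in change from baseline. That subtracts the whole chance baseline difference, when only a fraction r of it predicts the outcome. If the post hoc tests instead compare arms within a visit, a free-means model with complete data compares raw follow-up means and makes no use of baseline. Section 3.10 does not say which contrast is meant. Either way, the model estimates separately three quantities that the design makes equal.

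This matters in a small trial. With 22 children per arm and 20% expected attrition, about 17.6 per arm finish, so precision is scarce and chance baseline differences can be sizeable.

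The baseline tests are a separate matter. After concealed randomisation, a test of equal baseline means tests a hypothesis already known to be true. Its p-value neither measures the effect of an imbalance nor corrects it.

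**Working it through.** **Inputs.** From the article: three arms of 22, 20% attrition, two-sided 5%, three occasions, baseline before randomisation, and the planning effect ("The calculation considered an effect size of 0.87, derived from outcomes of the Canadian Occupational Performance Measure"). Assumed: r = 0.3 to 0.9, equal variances over time, and outcome SD = 1.

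**The plan's own figure.** The article gives no precision for the model, only a sample size. A two-sided two-sample t-test with d = 0.87 and 80% power needs 21.7, so 22 per arm and 66 in total, before any attrition. Whether attrition was allowed for is a separate question. Here it means only that there is little spare precision.

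**How baseline enters.** Suppose baseline were a covariate. The outcome would then have two occasions, and the interaction would test only whether the arms diverge between post-intervention and three months. An effect present at post-intervention and fully maintained would produce no interaction, so the post hoc tests would not be reached. The gate makes sense only if baseline is an outcome level.

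**Variance of a two-arm contrast at one follow-up, n per arm:**
- change from baseline: 2 × 2(1−r)/n
- raw follow-up means: 2/n
- common baseline mean, or baseline covariate: 2(1−r²)/n

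The ratios to the third line are 2(1−r)/(1−r²) = 2/(1+r) and 1/(1−r²).

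| r | Change, n = 22 | Raw, n = 22 | Common baseline, n = 22 | Change ÷ common | Raw ÷ common |
|---|---|---|---|---|---|
| 0.3 | 0.1273 | 0.0909 | 0.0827 | 1.54 | 1.10 |
| 0.5 | 0.0909 | 0.0909 | 0.0682 | 1.33 | 1.33 |
| 0.7 | 0.0545 | 0.0909 | 0.0464 | 1.18 | 1.96 |
| 0.9 | 0.0182 | 0.0909 | 0.0173 | 1.05 | 5.26 |

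For example, at r = 0.5 the change contrast is 2 × 2 × 0.5/22 = 0.0909 and the common-baseline contrast is 2 × 0.75/22 = 0.0682. Generalised least squares for three arms by three times, with a common correlation, gives the same values for the change and common-baseline columns. The common-baseline column is the smallest in every row.

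**Power, as illustration only.** This takes d = 0.87 in follow-up SD units, 17.6 completers per arm, one pairwise contrast at an uncorrected 5%, and 3n − 3 error degrees of freedom.

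| r | Change | Raw | Common baseline |
|---|---|---|---|
| 0.3 | 0.571 | 0.716 | 0.756 |
| 0.5 | 0.716 | 0.716 | 0.832 |
| 0.7 | 0.904 | 0.716 | 0.943 |
| 0.8 | 0.979 | 0.716 | 0.988 |

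With Bonferroni over three pairs at r = 0.5, the change contrast has power 0.545 and the common-baseline contrast 0.691.

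**The case against.** The strongest reply is that the article does not say baseline means are free. It is a condensed account, and covariates, mean constraints and covariance structure are often left to a fuller document. That stands: free means is an inference, though the interaction gate supports it strongly. A reader might also infer that the planned analysis is wrong or biased. It is not. A group-by-time model over three occasions is standard and unbiased under randomisation, so the point is one of efficiency.

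The size of the gain is also uncertain, and this too stands. The documents give no r for either primary outcome. The standardiser of 0.87 is not stated; if it were the SD of change, change-score power at 17.6 per arm would be about 0.72 whatever r is. The post hoc tests are gated and Bonferroni-corrected, and maximum likelihood keeps partial data, so the uncorrected completer powers are not the plan's powers.

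It is tempting to say that adjustment wins back most or all of the power lost to attrition. Twenty per cent attrition inflates variance by 1/0.8 = 1.25. Against a change-score contrast, adjustment offsets all of that only if 2/(1+r) is at least 1.25, that is, r of 0.6 or less. At r = 0.9 it offsets 5%.

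Finally, the baseline tests should not be blamed for lost precision. The article does not say that their results will alter the model. Nor does it tie the Shapiro–Wilk test to baseline in particular. None of these objections removes the core point: for any r strictly between 0 and 1, the common-baseline contrast is more precise than either version of the planned one.

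**Conclusion.** The point holds as a free improvement. On the natural reading, the planned contrast has more variance than it need have. The excess is 54%, 33%, 18% or 5% at r = 0.3, 0.5, 0.7 or 0.9 if the contrast is change from baseline, and 10%, 33%, 96% or 426% if it is raw follow-up means. These figures assume equal variances over time and complete data, and r itself is assumed. The power figures only illustrate the direction and should not be quoted as the trial's power. The planned analysis remains valid. The baseline tests are stated outright and are uninformative, which is a lesser and separate reporting fault.

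**What to change.** In section 3.10, state that baseline, post-intervention and three-month values are modelled together, with one baseline mean common to all arms, separate arm means at the two follow-ups, and unstructured covariance. State that the arm contrasts are estimated directly at post-intervention and at three months. Baseline as a covariate in a model of the two follow-ups is an acceptable alternative. In that case the interaction must not remain as the gate, for the reason given in the working.

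Replace the ANOVA and Kruskal–Wallis baseline comparisons with a descriptive table by arm. Age and support level may be added as covariates, but nothing in the article makes them necessary.

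The cost is a few sentences. No extra children, visits or measurements are needed, and SPSS mixed models can fit either version. The common-baseline model spends no extra degrees of freedom; a single baseline covariate spends one of about 60. The change should be made before outcome data are seen by arm.

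### Therapists are tied to arms by profession, at least for the contrasts against psychology, but the described analysis and sample size make no allowance for therapist variation, so those standard errors may be too small

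*Protocol article*

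**What the plan says.** Children are randomised one by one (Randomization and blinding): "Allocation will follow an individual randomization scheme into three groups: (I) MIG program, (II) conventional psychology, and (III) conventional physiotherapy". Each treatment is then delivered in person by a therapist.

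- **MIG arm** (MIG program): "The intervention will be delivered by physiotherapists with prior experience in MIG and additional training provided by an interdisciplinary team".
- **Psychology arm** (Conventional psychology): "Participants in this group will receive intervention delivered by psychology professionals".
- **Physiotherapy arm** (Conventional physiotherapy): the content and timing of sessions are described. The article does not say who delivers them, or whether those therapists also treat MIG children.

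No arm has a stated number of therapists or of children per therapist. Both comparator arms leave room for clinical adaptation to the individual child.

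The Data analysis section reads: "Linear mixed-effects models will be used to evaluate intervention effects over time, including group-by-time interaction terms". It does not describe the random effects. It also fixes the error level: "A two-sided significance level of 5% (*p* < 0.05) will be adopted for all analyses".

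The Sample size section states: "The sample size was set at 66 participants, distributed into three groups with 22 individuals in each group". Its inputs are "The calculation considered an effect size of 0.87, derived from outcomes of the Canadian Occupational Performance Measure", together with "a statistical power of 80%, a significance level of *α* = 5%, and an estimated attrition rate of 20% over time". No ICC, caseload or design effect is among them.

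**The concern.** Children treated by the same therapist share that therapist's skill, style and rapport, so their changes after baseline may be correlated even though they were randomised individually. When each therapist works in one arm only, the average of that arm's therapist effects becomes part of the arm mean. A model with group, time and their interaction alone estimates the residual variance from differences between children and largely misses this component. The arm difference then carries variance that its standard error does not count.

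The contrasts at risk are the two against psychology, because a psychologist cannot also be the treating physiotherapist. One of them, MIG versus psychology, is part of the primary objective. The consequences would be intervals that are too narrow, a false-positive rate above the stated level, and the chance that a strong or weak therapist is read as a programme effect. Bonferroni correction does not cure this: it adjusts for the number of comparisons, not for a standard error that is too small.

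**Working it through.** **1. The plan's own figure.** The inputs from the Sample size section are an effect size of 0.87, 80% power, 5% alpha and 20% attrition. I take 0.87 as a standardised mean difference, since the article does not name the metric or the test. A two-sided two-sample t-test needs 21.7 per arm, so 22 per arm and 3 × 22 = 66, with power 80.5% before attrition. A one-sided normal calculation gives 17 per arm, and 17/(1 − 0.2) = 21.25, again 22. Both routes assume independent children. (How attrition enters the 66 is a separate question.)

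**2. Design effect.** With k therapists per arm and caseload m = 22/k, the variance of an arm mean is multiplied by DE = 1 + (m − 1) × ICC. The naive standard error is 1/√DE of the correct one. Both k and the ICC are assumptions.

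Example with k = 2 and ICC 0.05: m = 11, DE = 1 + 10 × 0.05 = 1.50 and 1/√1.50 = 0.82. The standard error is understated by about 18%.

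**3. True size of a nominal two-sided 5% pairwise test.** There were 40,000 simulated trials per cell, with 22 children per arm, one therapist per child, therapists nested in arms, total variance 1 and no true effect. The test is a t-test that ignores therapist.

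| Therapists per arm | m | DE at ICC 0.05 | SE ratio at ICC 0.05 | Size, ICC 0.01 | Size, ICC 0.05 | Size, ICC 0.10 |
|---|---|---|---|---|---|---|
| 2 | 11 | 1.50 | 0.82 | 6.2% | 11.3% | 17.3% |
| 3 | 7.3 | 1.32 | 0.87 | 5.7% | 8.8% | 12.8% |
| 4 | 5.5 | 1.23 | 0.90 | 5.5% | 7.7% | 10.5% |
| 6 | 3.7 | 1.13 | 0.94 | 5.3% | 6.7% | 8.3% |

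Simulation error is about 0.1 to 0.2 percentage points. At ICC 0 the size is 5% in every row. If 20% are lost (22 × 0.8 = 17.6, taken as 18 per arm), two therapists per arm give 10.0% at ICC 0.05 and 14.8% at ICC 0.10.

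**4. Closer to the planned testing.** At ICC 0.05 the three-arm F-test has a size of 13.7%, 10.4% and 9.0% for 2, 3 and 4 therapists per arm. If pairwise tests follow only a significant F-test and are Bonferroni-corrected, the family-wise rate at 2 per arm and ICC 0.05 is still about 11% to 12%, depending on how the variance is pooled. This approximates the three-visit mixed model by a single change score.

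**5. Counter-case: shared therapists.** If the same physiotherapists treat both motor arms and have the same effect in each, the size for MIG versus physiotherapy is 4.2% to 4.9%, which is not inflated.

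**6. Power with a correct standard error.** By the normal approximation at 22 per arm, an effect of 0.87 gives 0.87/√(2/22) = 2.885, and 2.885 − 1.96 = 0.925, so 82%. With DE 1.50: 2.885/1.225 − 1.96 = 0.40, so 65%. For 3, 4 and 6 therapists per arm at ICC 0.05 it is 71%, 74% and 77%. A therapist-level t-test, which also pays for its few degrees of freedom, has 28%, 48%, 59% and 69% for 2, 3, 4 and 6 per arm.

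**The case against.** The strongest reply is that silence is being read as a statement. The article does not say that children are treated as independent. It names a mixed model, lists the interaction as something included, and describes no random effects at all, not even one for the child. That level of detail is often left to the full protocol or analysis plan. This stands: a reader might infer that the planned model assumes independence between children of the same therapist, but the text does not establish it. What remains is that the sample-size inputs are listed and contain no clustering allowance, and that recording therapists and balancing caseloads must happen during delivery. A later analysis plan cannot create them.

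Second, a reader might extend the point to all three contrasts. The documents do not support that. Who delivers conventional physiotherapy is not stated, and shared therapists could remove the inflation for MIG versus physiotherapy. Nesting by profession is secure only against psychology.

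Third, the size rests on assumptions. The article uses the plural for the MIG and psychology therapists but gives no numbers, and does not say that each child keeps one therapist. Spreading a child's sessions over several therapists could dilute the clustering. Therapist training, the weekly activity table, the scripted psychology sessions and the timed physiotherapy blocks may all keep the ICC low. This also stands, and is why a range is shown.

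Fourth, a therapist random effect estimated from two to four therapists per arm is unstable and costs much power. Whether to generalise beyond the trial's own therapists is also partly a choice of inference target. This is a fair argument against changing the primary model, but not against a sensitivity analysis.

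**Conclusion.** The point holds in a limited form. For the two contrasts against psychology, therapist and arm are tied together by design. Neither the described model nor the sample size allows for therapist variation. If it exists and is left out, those standard errors are too small.

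The size is uncertain. It runs from about 5% to 17% for a nominal 5% pairwise test over 2 to 6 nested therapists per arm and ICC 0.01 to 0.10. With 4 to 6 therapists per arm and ICC 0.01 it is negligible (5.3% to 5.5%); with 2 per arm and ICC 0.05 or more it is at least double the nominal level. A reader might conclude that the trial's 5% level is certainly not held. The documents do not support that, because they give neither the ICC nor the caseloads, and at ICC 0 nothing is lost.

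The change is worth making because it is cheap, affects what can be concluded about MIG versus psychology, and partly cannot be done afterwards.

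**What to change.** **During delivery.** Record the treating therapist at every session. Spread each arm's children evenly over the therapists already available. State how many therapists serve each arm and whether any work in two. If delivery is already complete, the balancing is no longer possible and only the recording and reporting remain.

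**In the analysis.** Keep the primary model. Pre-specify a sensitivity analysis of both primary outcomes that adds a therapist effect acting on the two post-baseline visits only, since all baselines precede randomisation. Use small-sample degrees of freedom (Satterthwaite or Kenward-Roger) and report the estimated ICC.

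**Where an arm has too few therapists to estimate that variance.** Report the contrasts with intervals inflated for ICC 0.01, 0.05 and 0.10, and state that therapist and programme effects cannot be separated. For equal caseloads the half-width is multiplied by √DE. With 11 children per therapist this is √1.10 = 1.05, √1.50 = 1.22 and √2.00 = 1.41. With one therapist for all 22 it is √1.21 = 1.10, √2.05 = 1.43 and √3.10 = 1.76.

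**Cost.** One data field per session, some scheduling effort and one additional analysis. The drawbacks are wider intervals, a poorly estimated therapist variance and low power in that analysis when therapists are few. That is why it should sit beside the primary model and not replace it.
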